## Abstract

**Background:**

Single-pass, contrast-enhanced whole body multidetector computed tomography (MDCT) emerged as the diagnostic standard for evaluating patients with major trauma. Modern iterative image algorithms showed high image quality at a much lower radiation dose in the non-trauma setting. This study aims at investigating whether the radiation dose can safely be reduced in trauma patients without compromising the diagnostic accuracy and image quality.

**Methods/Design:**

Prospective observational study with two consecutive cohorts of patients.

*Setting:* A high-volume, academic, supra-regional trauma centre in Germany.

*Study population:* Consecutive male and female patients who 1. had been exposed to a high-velocity trauma mechanism, 2. present with clinical evidence or high suspicion of multiple trauma (predicted Injury Severity Score [ISS] ≥16) and 3. are scheduled for primary MDCT based on the decision of the trauma leader on call.

*Imaging protocols:* In a before/after design, a consecutive series of 500 patients will undergo single-pass, whole-body 128-row multi-detector computed tomography (MDCT) with a standard, as low as possible radiation dose. This will be followed by a consecutive series of 500 patients undergoing an approved ultra-low dose MDCT protocol using an image processing algorithm.

*Data:* Routine administrative data and electronic patient records, as well as digital images stored in a picture archiving and communications system will serve as the primary data source. The protocol was approved by the institutional review board.

*Main outcomes:* (1) incidence of delayed diagnoses, (2) diagnostic accuracy, as correlated to the reference standard of a synopsis of all subsequent clinical, imaging, surgical and autopsy findings, (3) patients’ safety, (4) radiation exposure (e.g. effective dose), (5) subjective image quality (assessed independently radiologists and trauma surgeons on a 100-mm visual analogue scale), (6) objective image quality (e.g., contrast-to-noise ratio).

*Analysis:* Multivariate regression will be employed to adjust and correct the findings for time and cohort effects. An exploratory interim analysis halfway after introduction of low-dose MDCT will be conducted to assess whether this protocol is clearly inferior or superior to the current standard.

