### Design history and IRB concerns

The study was originally planned as non-inferiority randomized controlled trial (NI-RCT) with the following hypotheses:

*Null hypothesis* H_0_ notated as:

$$H_{0}:C-T\geq M\;\left(C\;\mathrm{is}\;\mathrm{superior}\;\mathrm{to}\;T\right)$$

where C = image quality in the standard-of-care arm, T = image quality in the experimental (iDose) arm, and M = non-inferiority margin

*Alternative hypothesis* H_A_ expressed as

$$H_{A}:C-T<M\;\left(T\;\mathrm{is}\;\mathrm{not}\;\mathrm{inferior}\;\mathrm{to}\;C\right)$$

In *clinical terms*, the primary hypothesis read as:

In patients with multiple trauma scheduled for single-pass, contrast-enhanced whole-body 128-row MDCT, the iDose algorithm will generate a subjective image quality rated on a visual analogue scale (0 – 100 mm) which is not inferior to standard image production and processing.

The non-inferiority margin (NIM) was set at 1 mm, with a standard deviation of 4 mm (derived from a pilot study of 2 × 20 patients). The sample size for a non-inferiority trial of two means was computed using PASS 11.0 software (NCSS, LLC. Kaysville, Utah, USA). For a fixed NIM of 1 mm, the needed sample size per group was 253 patients to confirm non-inferiority of the experimental compared to the control intervention with a one-sided alpha 0.025 and a power of 80%.

The protocol was submitted to the institutional review board (IRB) of the Charité University Medical Centre, Berlin, Germany, in May 2013. It accounted for 1. the inclusion of unconscious and minor patients in an emergency setting (with distinct processes of informing relatives and deferred informed consent procedures) and 2. varying exposure to radiation for diagnostic purposes as the intervention of interest. Given that MDCT trauma imaging at a lower than usual radiation dose is not the current standard of care in Germany, the institutional review board issued concerns that patients in the experimental group are at risk of missed injuries (not that patients in the standard-of-care group may be exposed to a higher than needed effective dose). Consequently, the initial proposal was rejected. A revised proposal submitted in June 2013 could not solve the IRB’s concerns.

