Consequently, the investigators changed their approach to comply with the IRB’s recommendations, and consented on a before/after cohort study. All patients in this study will receive an accepted diagnostic standard of care using approved technologies but will not undergo random allocation to either modality. One may still argue that injuries are acute, unforeseeable events, and there remains a random component in the study set-up.

The ultimate consequence of shifting from an experimental to an observational design was the increase in the sample size to allow for robust multivariate modelling and adjustment of results for confounding.

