### Primary outcome

Delayed diagnoses comprise pathological anatomic and / or physiologic findings which demand clinical awareness, or, in case of therapeutically relevant pathological results, should prompt immediate therapeutic action.

We will estimate the incidence of delayed diagnoses based on a synopsis of all subsequent clinical, imaging, intra-operative, and autopsy findings until discharge. We will further distinguish between clinically relevant and all diagnoses. Relevant diagnoses are defined as severe injuries suiting an Abbreviated Injury Scale [AIS] score ≥3 and/or injuries demanding surgical and/or trans-vascular intervention. Non-traumatic incidental findings like tumours or tumour-like lesions demanding specific work-up and/or treatment will be recorded in an exploratory attempt.

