#### Safety

Any situation in which the individual patient’s safety is assumed to be compromised will be recorded and evaluated in a cumulative fashion. Safety-relevant events will be entered in the local Critical Incident Reporting System (CIRS), hosted by the Medical Council (Ärztekammer) of Berlin, Germany. Since this is an observational study, we will use common definitions of adverse events (AE), serious adverse events (SAE), and Suspected Unexpected Serious Adverse Reactions (SUSAR), as outlined in ICH Topic E2B (Clinical Safety Data Management: Data Elements for Transmission of Individual Case Safety Reports), and most recently in the amended and updated DIN-ISO 14155 guideline, but do not implement a regular reporting procedure.

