### Sample size considerations and calculations

The sample size is calculated to guarantee a certain precision of a range of estimates, not to achieve a certain power to detect an *a priori* defined effect size.

With 500 eligible cases in either cohort, this study fulfils the following prerequisites:

1. 95% confidence intervals of both risk and mean differences must not exceed the point estimate by more than 5% in either direction

2. multivariate modelling must be possible for five independent covariates (respecting Harrell’s rule)

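### Patient safety is compared between two consecutive cohorts on judgement-triggered incident records without regular reporting, so recording may differ with the protocol in use; the abstract's interim look also needs reconciling with the body

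*Protocol article*

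**What the plan says.** Safety is the third of the main outcomes in the Abstract and the third of the Objectives; in the body it stands under Secondary outcomes. It is to be evaluated with either protocol, that is, in 500 standard-dose patients and then 500 low-dose patients.

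The Safety section makes the trigger for a record any situation in which a patient's safety is thought to be at risk. Records are assessed cumulatively, and safety-relevant events go into the local Critical Incident Reporting System (CIRS). Common definitions of adverse and serious adverse events apply, but, citing the observational design, the authors "but do not implement a regular reporting procedure".

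The primary outcome is collected differently: "We will estimate the incidence of delayed diagnoses based on a synopsis of all subsequent clinical, imaging, intra-operative, and autopsy findings until discharge".

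On interim analysis, the Abstract says: "An exploratory interim analysis halfway after introduction of low-dose MDCT will be conducted", and gives its purpose as "to assess whether this protocol is clearly inferior or superior to the current standard". Neither Sample size considerations and calculations nor Analysis plan mentions such a look.

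**The concern.** An outcome compared between cohorts has to be ascertained in the same way in both. Here the trigger is a judgement by someone at the centre. The protocol in use changes for all patients at one point in time, and the article does not say that treating staff are unaware of it. Staff who know that a reduced-dose scan is new may report more readily, which would make low dose look harmful. They may also report less as the study goes on, which would hide harm. Regression on patient covariates cannot remove either effect, because the fault lies in the measurement and coincides with the exposure.

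The stakes are specific to this study. When it judged the randomised design, "the institutional review board issued concerns that patients in the experimental group are at risk of missed injuries". Readers will look to the safety comparison for an answer on harm, and a ratio of incident reports is poor evidence on that.

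The interim look is a smaller matter. The Abstract promises a verdict in either direction, and the body's analysis sections do not carry it. If the look is made and shows nothing, it may be taken as reassurance that it cannot give.

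**Working it through.** **1. The plan's own figures.** No figure is stated for the safety comparison or the interim look. The one sample size with full inputs, 253 per group (margin 1 mm, SD 4 mm, one-sided 0.025, power 80%), belongs to the abandoned randomised design. It reproduces (252 by normal approximation, 253 by the noncentral t) and has no bearing here. The current size is set for precision, "not to achieve a certain power to detect an" effect size fixed in advance.

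**2. Safety recording.** Compare the two routes to an event:

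| | Delayed diagnoses (Primary outcome; Recruitment and documentation) | Safety (Safety section) |
|---|---|---|
| Source | all clinical, imaging, operative and autopsy findings | situations judged to put the patient at risk |
| Trigger | a finding in the record | a person's judgement |
| Window | until discharge | none stated |
| Regular procedure | synopsis for every patient | regular reporting not implemented |

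Let p be the true event risk and r the probability that an event is recorded, with S for standard and L for low dose. The recorded rate is p × r, so

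recorded ratio = (p_L / p_S) × (r_L / r_S).

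If the protocols are equally safe, the recorded ratio equals r_L / r_S, which is purely a recording effect. The article gives no value for r and no means of estimating it, so neither the direction nor the size of the bias can be fixed. A rule that finds events in the records without anyone having to report them brings r_L / r_S close to 1.

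**3. What a non-significant interim look would mean.** Assumptions: halfway means 250 of the 500 low-dose patients, compared with all 500 standard-dose patients; the endpoint is a proportion; the event rates are illustrative, because the article gives none.

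- Information fraction: (1/500 + 1/500) / (1/500 + 1/250) = 0.004/0.006 = 0.667.
- Unpooled SE for 5% v 10%: √(0.05×0.95/500 + 0.10×0.90/250) = √0.000455 = 0.02133.
- Pooled SE under no difference: p̄ = (25+25)/750 = 0.0667; √(0.0667×0.9333×0.006) = 0.01932.
- Power at two-sided 5%, unpooled: Φ(0.05/0.02133 − 1.96) = Φ(0.384) = 65%.
- The same, pooled: Φ((0.05 − 1.96×0.01932)/0.02133) = Φ(0.569) = 72%.
- One-sided O'Brien-Fleming-type spending of 0.025 at 0.667: 2×(1 − Φ(2.2414/0.8165)) = 0.006, so z = 2.512. Power is Φ(2.344 − 2.512) = 43% unpooled and Φ((0.05 − 2.512×0.01932)/0.02133) = 53% pooled.

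The same formulas for other assumed doublings give:

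| Assumed rates | Two-sided 5% (unpooled–pooled) | One-sided p<0.006 (unpooled–pooled) |
|---|---|---|
| 2% to 4% | 30–37% | 14–21% |
| 5% to 10% | 65–72% | 43–53% |
| 10% to 20% | 94–95% | 84–88% |

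Unless the baseline rate is fairly high, the look would often miss a doubling.

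**4. Error rate.** If both looks were read as two-sided 5% tests, the overall type I error would be 7.7% (bivariate normal, correlation √0.667). The article does not state that they will be.

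**The case against.** The strongest reply on safety is that the authors waive only a regular reporting procedure, which may mean formal reporting of adverse events. They keep cumulative evaluation, CIRS entry and standard definitions. That is true, and it is more than chance reporting. But standard definitions do not make recording complete or equal, and the trigger is still a judgement made by staff who are not said to be blinded.

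On the interim, the reply is largely right. The look is called exploratory, the sample size is precision-based with no stated alpha, and an article commonly leaves endpoint and boundary to a fuller document. Figure 1, the study flow, is not shown either. The lack of a numerical boundary is therefore not a fault in this text. What stands is that the Abstract announces a comparative look that the body's analysis sections omit, while the Discussion expects quasi-confirmatory inferences.

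Two stronger readings are tempting and unsupported. A reader might infer that the review board's missed-injury concern is left uncontrolled. The documents do not support this: missed or delayed diagnosis is the primary outcome, it is ascertained by the same synopsis in both cohorts, the design was changed on the board's advice, and the protocol was approved. A reader might also see a contradiction between the statement that lower-dose trauma imaging is not the current German standard and the statement that "All patients in this study will receive an accepted diagnostic standard of care using approved technologies". A technique can be accepted and approved without being the prevailing standard.

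**Conclusion.** The point holds for the safety comparison. As described, it rests on judgement-triggered records without regular reporting, in a before/after design with no stated blinding of treating staff, so it is open to differential recording of unknown direction and size. This assumes that staff know which protocol is in use, which is likely after a change in routine practice but is not stated. The primary outcome does not depend on these reports and is not affected by this point.

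The interim point is secondary: Abstract and body should agree. The power figures rest on a 500 v 250 split and assumed event rates; they show only that a non-significant look is not evidence of safety. The 7.7% is conditional on two formal 5% tests that the article does not specify, so it is not a demonstrated inflation.

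**What to change.** **Safety.** Base the between-cohort comparison on objective events, for example in-hospital death and unplanned re-operation or intervention for a delayed diagnosis. Extract them by one written rule from the routine records of both cohorts over the same window, and keep CIRS entries as a descriptive supplement. The records are already the study's data source, so the cost is some extra extraction work.

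**Interim.** Either carry the look into Analysis plan and Sample size considerations and calculations, or reconcile the Abstract sentence with them. If it is kept, tie it to clinically relevant delayed diagnoses as defined under Primary outcome, say what clearly inferior or superior means, keep the promised adjustment for time and cohort effects, and state that a non-significant look is not evidence of safety. This costs only wording. If a strict threshold such as one-sided p<0.006 is chosen, its lower power should be reported beside it.

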**Discussion:**

Although non-experimental, this study will generate first large-scale data on the utility of imaging-enhancing algorithms in whole-body MDCT for major blunt trauma.

**Trial registration:**

Current Controlled Trials ISRCTN74557102.

## Background

According to the most recent injury statistics, every two minutes someone dies of an injury in the European Union [1]. Trauma is, and will remain a significant contributor to years of productive life lost, disability, and health care service costs worldwide [2-4].

The survival and functional prognosis of patients who suffered severe and multiple injuries improved significantly in the industrialized countries [5-8]. Time to appropriate care is an accepted predictor of trauma outcomes, and transport, triage, and work-up intervals must respect this decisive factor. Also, immediately life-threatening injuries and sources of bleeding must be identified (or excluded) with high accuracy [9,10]. Apart from damage-control resuscitation and surgery, the introduction of contrast-enhanced, whole-body, multi-detector computed tomography may be regarded as one of the most important interventions which changed the face of trauma care during the past decade [11-14].

In a recent survey of UK emergency departments, 41 out of 184 (22.3%) respondents indicated that they had a pan-scan policy for major trauma patients, with marked regional variations in availability and reporting times [15]. Data from the German TraumaRegister^D^ suggest that incorporating a routine pan-scan into trauma resuscitation may increase the ratio of observed to expected survivors [16]. A recent analysis confirmed the results in a subsequent cohort and unstable patients [17]. Yet, many injuries to solid organs (e.g., brain, liver, spleen) demarcate only after sufficient resuscitation with crystalloid fluids and blood products. We recently demonstrated in a large cohort of 982 patients that an initial pan-scan is capable to prove but not to exclude injuries to various body regions [18].

Opponents of the whole-body scan have been voicing concerns about patients’ overexposure to radiation with the increasing and often uncritical use of this technology [19-24].

Exposure to radiation for diagnostic purposes is an emerging ethical, medico-legal and public-health issue [25]. It has been estimated that, with the widespread and liberal use of CT, 1.5 - 2.0% of all cancers in the US may now be attributable to the radiation from CT examinations [21]. The median lifetime attributable risk (LAR) of cancer is 4.0 (IQR 0.8 - 11.1) / 1000 for a multiphase abdomen and pelvis CT scan [26].

Modern 64-, 128- and 256-row MDCT scanners are regarded to produce lower dose indexes (CTDI_vol_) than earlier generation single- or 4-row hardware. However, Harrieder et al. recently demonstrated in a retrospective study that, because of enhanced scan lengths, the dose-length-product (DLP) may remain similar or even increase with modern hardware [27]. The authors, however, provided little information on patient demographics (e.g., BMI, ISS) and did not only compare different multi-detector-row technologies but also scanners made by different manufacturers. A comparison of 64-row scanners of four leading companies suggested highest patient mean effective doses (in mSv) produced by the GE LightSpeed VCT (12.7 ± 2.6), followed by the Toshiba Aquilion (11.1 ± 3.3), Philips Brilliance (9.5 ± 0.4) and Siemens Somatom (9.1 ± 1.1) [28].

So-called adaptive statistical iterative algorithms (ASIR), derived from a Bayesian framework, incorporate i. random fluctuations in sinogram measurements [29], ii. non-ideality, iii. different degrees of data credibility, iv. *a priori* information about the distribution of the image space, and other previously unconsidered variables to enhance resolution and reduce artefacts and noise [30].

Distinct technologies like Veo (Model Based Image Reconstruction, GE Healthcare) or IRIS (Iterative Reconstruction in Image Space, Siemens) received FDA approval [31].

Apart from phantom studies and smaller case series, there is currently sparse evidence from head-to-head studies about the effect of ASIR technology on objective and subjective image quality, and exposure to radiation. Exemplarily, Prakash et al. from Boston showed in a cohort of 222 patients who had previously undergone abdominal CT with filtered back projection (FBP) technology and were scheduled for follow-up ASIR scan that CTDL_vol_ and DLP were markedly reduced without compromising image quality [32]. The Prakash group showed similar results in chest CT [33,34]. Other investigators reported similar dose reductions with similar image quality in CT portovenography [35], cerebral CT [36], and abdomino-pelvic CT scans [37].

There is evidence from phantom tests and rigorous clinical evaluations with global clinical collaborators which demonstrate the potential of the FDA-approved iDose system (Philips Healthcare, Eindhoven, The Netherlands) to improve image quality and / or lower radiation dose levels beyond those previously achievable with conventional, routine-dose acquisitions, or FBP reconstructions [38-43].

The combination of BMI-adapted protocols with iterative reconstruction algorithms can reduce radiation exposure to patients and simultaneously improve image quality [38].

Previous non-trauma / elective CT investigations suggest that iterative reconstruction algorithms may maintain image quality at a much lower radiation dose. Yet, large-scale, prospective evidence on the safety and effectiveness of low-dose CT in trauma patients is still sparse. A single retrospective study investigated possible dose reduction at maintained image quality in subjects with multiple injuries [44]. Since results were not adjusted for baseline imbalances (e.g., a 7% difference in the prevalence of comorbidity), conclusions and inferences from this study are difficult to interpret.

Patients with multiple injuries are typically young and thus at a higher risk of CT-induced cancer. Reducing exposure to radiation with constant image quality and diagnostic accuracy in this vulnerable cohort is a key goal of trauma services worldwide, and evidence whether imaging at lower doses of radiation is feasible, safe, and effective is needed. On the other hand, it may be argued that, given the proven benefit of MDCT in lowering trauma-associated mortality, the primary scan must exhaust the full potential of the method and should aim for maximum quality of images to avoid false-negative results, regardless of exposure to radiation.

## Methods/Design

### Design

The Dose Reduction in whole-body computed tomography of Multiple Injuries (DoReMI) investigation is a prospective cohort study employing two large, consecutive cohorts of patients undergoing different approved and established MDCT protocols. All data will be recorded, stored and processed under the conditions of daily practice of trauma care. Gathered data will form the basis for a later interrupted time-series comparison between the effectiveness and safety of the scanning protocols.

### Design history and IRB concerns

The study was originally planned as non-inferiority randomized controlled trial (NI-RCT) with the following hypotheses:

*Null hypothesis* H_0_ notated as:

$$H_{0}:C-T\geq M\;\left(C\;\mathrm{is}\;\mathrm{superior}\;\mathrm{to}\;T\right)$$

where C = image quality in the standard-of-care arm, T = image quality in the experimental (iDose) arm, and M = non-inferiority margin

*Alternative hypothesis* H_A_ expressed as

$$H_{A}:C-T<M\;\left(T\;\mathrm{is}\;\mathrm{not}\;\mathrm{inferior}\;\mathrm{to}\;C\right)$$

In *clinical terms*, the primary hypothesis read as:

In patients with multiple trauma scheduled for single-pass, contrast-enhanced whole-body 128-row MDCT, the iDose algorithm will generate a subjective image quality rated on a visual analogue scale (0 – 100 mm) which is not inferior to standard image production and processing.

The non-inferiority margin (NIM) was set at 1 mm, with a standard deviation of 4 mm (derived from a pilot study of 2 × 20 patients). The sample size for a non-inferiority trial of two means was computed using PASS 11.0 software (NCSS, LLC. Kaysville, Utah, USA). For a fixed NIM of 1 mm, the needed sample size per group was 253 patients to confirm non-inferiority of the experimental compared to the control intervention with a one-sided alpha 0.025 and a power of 80%.

The protocol was submitted to the institutional review board (IRB) of the Charité University Medical Centre, Berlin, Germany, in May 2013. It accounted for 1. the inclusion of unconscious and minor patients in an emergency setting (with distinct processes of informing relatives and deferred informed consent procedures) and 2. varying exposure to radiation for diagnostic purposes as the intervention of interest. Given that MDCT trauma imaging at a lower than usual radiation dose is not the current standard of care in Germany, the institutional review board issued concerns that patients in the experimental group are at risk of missed injuries (not that patients in the standard-of-care group may be exposed to a higher than needed effective dose). Consequently, the initial proposal was rejected. A revised proposal submitted in June 2013 could not solve the IRB’s concerns.

Consequently, the investigators changed their approach to comply with the IRB’s recommendations, and consented on a before/after cohort study. All patients in this study will receive an accepted diagnostic standard of care using approved technologies but will not undergo random allocation to either modality. One may still argue that injuries are acute, unforeseeable events, and there remains a random component in the study set-up.

The ultimate consequence of shifting from an experimental to an observational design was the increase in the sample size to allow for robust multivariate modelling and adjustment of results for confounding.

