## Discussion

This is the first study which assesses the potential value of a dose-reducing MDCT regimen in patients with multiple and severe trauma. The investigators initially planned a RCT which was rejected by the local IRB.

The current protocol aims at balancing regulatory and methodological issues. While the present study (because of its non-experimental design) cannot formally prove that low-dose MDCT is feasible, safe, and evenly accurate compared to normal-dose MDCT in the trauma setting, the cohort size, the setting, and the anticipated characteristics of patient cohorts will guarantee both high internal and external validity of findings. Advanced statistical approaches will allow for quasi-confirmatory inferences. In the absence of large-scales RCTs, this study may provide the best available evidence to decide in favour of one or the other diagnostic approach.

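### The stated precision of 500 per cohort ignores that cohort is a step function of calendar time: a linear or segmented trend adjustment raises the variance about 4-fold, more than the larger sample gains

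*Protocol article*

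**What the plan says.** Under Design history and IRB concerns, the protocol article describes a randomised non-inferiority trial on subjective image quality for which "the needed sample size per group was 253 patients". The review board rejected it. The investigators then chose a before/after study and name as the main consequence "the increase in the sample size to allow for robust multivariate modelling and adjustment of results for confounding".

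The Abstract puts 500 standard-dose patients first and 500 low-dose patients after them, and adds: "Multivariate regression will be employed to adjust and correct the findings for time and cohort effects". The Design section says the data will serve "a later interrupted time-series comparison between the effectiveness and safety of the scanning protocols", and the Analysis plan refers to time-series models.

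The section Sample size considerations and calculations justifies 500 per cohort by precision, not power. It gives two criteria: 95% confidence intervals for risk and mean differences that go no more than 5% beyond the point estimate on either side, and room for five covariates. It does not say whether this precision is meant before or after adjustment for time.

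The Discussion concludes that "the cohort size, the setting, and the anticipated characteristics of patient cohorts will guarantee both high internal and external validity of findings".

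**The concern.** With a single switch and no overlap, knowing the scan date is enough to know the cohort. A model with both a cohort indicator and a time trend must separate two nearly collinear terms, and the cohort effect loses precision. The sample size section makes no allowance for this, although time adjustment and an interrupted time series are the analyses the protocol names.

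The primary outcome is delayed diagnoses, and missed injuries were the review board's worry. If readers credit the adjusted result with the precision of a plain comparison of 500 with 500, an interval that still contains a sizeable increase in delayed diagnoses may be taken as reassurance. If the analysts instead rely on the narrow unadjusted contrast, any change over calendar time is mixed with the change of scan protocol.

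**Working it through.** **Inputs from the protocol.** Original sizing: margin 1 mm, SD 4 mm, one-sided alpha 0.025, power 80%, 253 per group. Current sizing: 500 per cohort, consecutive, precision criterion 5%.

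**Assumptions.** True difference 0 in the original sizing. Even accrual within each cohort and no gap unless stated. The 5% is read as percentage points; as a relative figure it could not be met for small differences (a risk difference of 2 points would need a half-width of 0.1 point). Incidence of delayed diagnoses is varied because none is given.

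**Step 1. Reproduce 253.** Normal approximation: n = 2 × 4² × (1.960 + 0.842)² / 1² = 251.2, so 252. With the noncentral t distribution, power is 79.98% at 252 and 80.14% at 253. The stated 253 reproduces. Going from 253 to 500 multiplies information by 500/253 = 1.98.

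**Step 2. Variance factor for a common linear trend.** Let the cohorts last L1 and L2 with a gap g between them.

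- Variance of time between cohorts: (L1 + L2 + 2g)² / 16
- Variance of time within cohorts: (L1² + L2²) / 24
- Variance factor for the cohort effect: 1 + between/within = 1 + 1.5 × (L1 + L2 + 2g)² / (L1² + L2²)

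| Layout | Factor | 500 / factor |
|---|---|---|
| Equal durations, no gap | 1 + 1.5 × 4/2 = 4.0 | 125 |
| 1 : 0.5 or 1 : 2 | 1 + 1.5 × 2.25/1.25 = 3.7 | 135 |
| 1 : 0.1 | 1 + 1.5 × 1.21/1.01 = 2.8 | 179 |
| Limit, one cohort very short | 1 + 1.5 = 2.5 | 200 |
| Equal durations, gap of a quarter of a cohort | 1 + 1.5 × 6.25/2 = 5.7 | 88 |

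For equal durations, the squared correlation of cohort with time is 0.75, and 1/(1 − 0.75) = 4. Inverting the design matrix for 500 + 500 patients gives the same values. A segmented model (level change at the switch, separate slopes) also gives 4.0, at any ratio of durations without a gap. A cubic trend with equal durations gives 7.1. In a logistic model near the null, the information matrix gives 4.0, and a simulation at 10% incidence gives 3.7. Every trend layout shown exceeds the break-even of 1.98.

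**Step 3. Set this against the 5% criterion.** The half-width of the 95% interval for the risk difference is 1.96 × √(2p(1 − p)/500), multiplied by √4 = 2, or by √2.5 = 1.58 in the most favourable limit.

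| Incidence p (assumed) | Unadjusted | Factor 2.5 | Factor 4 |
|---|---|---|---|
| 4% | 2.4 points | 3.8 | 4.9 |
| 5% | 2.7 | 4.3 | 5.4 |
| 10% | 3.7 | 5.9 | 7.4 |
| 20% | 5.0 | 7.8 | 9.9 |

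The criterion is met when p(1 − p) ≤ 250 × (0.05/1.96)² / factor = 0.163 / factor. That gives p up to about 20% unadjusted, about 7% at factor 2.5 and about 4% at factor 4.

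**Mean differences.** With SD 4 mm, the half-width for the image-quality scale goes from 1.96 × 4 × √(2/500) = 0.50 mm to 0.99 mm. Both are inside 5 mm on a 100-mm scale, so the difficulty lies with the risk difference.

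**The case against.** **The form of the time term is not fixed.** This is correct, and leaving it to an analysis plan is no fault. Seasonal terms alone, over cohorts of whole years, give a factor of about 1.0. Random month effects without a trend (12 months per cohort assumed) bring 500 below the equivalent of 253 only at an intraclass correlation of about 0.025 or more. The loss is therefore conditional on fitting a trend. But those alternatives leave a secular trend uncorrected, and an interrupted time series normally models one.

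**A reader might infer that the protocol claims 500 consecutive patients replace 253 randomised ones, and that the claim fails.** The documents do not support this reading. The protocol says only that the increase allows modelling and adjustment; it nowhere equates the two designs. A reader might also work out power on the 1 mm margin (about 80% with 253 concurrent, 98% with 500 unadjusted, about 50% with 500 trend-adjusted) or the number per cohort needed to match the trial. Those figures concern a hypothesis on image quality that the study has abandoned. The primary outcome is now delayed diagnoses, and the sample size section disclaims power. Only the variance factor carries over, because it depends on the layout of the cohorts and hardly on the outcome.

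**A trend-adjusted estimate need not be the better one.** This also stands. Without a trend, adjustment gives away up to three quarters of the information. With a non-linear trend, a linear term leaves bias. Neither estimate separates the scan protocol from other changes made at the switch. The choice is a trade between bias and variance, so it would be wrong to make the trend-adjusted estimate the sole basis for conclusions.

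**The limitation is disclosed.** The Discussion concedes that a non-experimental study cannot give formal proof, and it rests validity on three grounds, not on size alone. Yet the same sentence goes on to promise high internal validity, and more patients do not remove confounding with time.

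**Conclusion.** The concern holds in conditional form. If the planned adjustment contains a linear or segmented time trend, the variance of the scan-protocol effect rises about 4-fold at even accrual, about 2.5 to 4-fold for unequal durations under a common linear trend, and further with a gap or a non-linear trend. For the no-gap linear or segmented case, 500 per cohort then carry the information of roughly 125 to 200 concurrent patients per arm. The near-doubling from 253 does not cover that loss.

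The stated 5% precision, read as percentage points, holds for the unadjusted risk difference up to about 20% incidence. After trend adjustment it holds only up to about 4% at even accrual, or about 7% in the most favourable limit. Incidence and accrual pattern are assumptions, since the protocol gives neither. The design was imposed by the review board and is not faulted here; what needs correcting is the precision and validity claimed for it.

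**What to change.** Keep 500 per cohort.

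1. In Sample size considerations and calculations, say that the 5% precision refers to the unadjusted contrast. Beside it, give the expected half-widths of the trend-adjusted risk difference over a range of incidences (for example 5.4, 7.4 and 9.9 points at 5%, 10% and 20%), labelled with the assumptions of even accrual, adjacent cohorts and a linear trend.
2. In Design history and IRB concerns, qualify the claim of robust adjustment: under those assumptions, adjusting for a trend costs about a factor of 4 in variance.
3. In the Discussion, remove cohort size from the grounds that guarantee internal validity. Commit to reporting the unadjusted and trend-adjusted estimates side by side, and state that increases in delayed diagnoses lying inside the adjusted interval cannot be excluded.

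This takes a few sentences and a short table. It needs no further patients, no new data and no change to imaging or care. The downside is that the stated precision becomes less favourable.
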